## Backgrounds

The number of patients on maintenance dialysis is increasing worldwide. Diabetic nephropathy and hypertensive kidney disease account for most of these patients. Chronic kidney disease (CKD) is an independent risk factor for cardiovascular disease (CVD) [1–5]. Moreover, CVD, which leads to difficulty with dialysis therapy, is strongly associated with higher mortality. Coronary heart disease is a typical condition among CVDs. However, aortic stenosis (AS) is increasingly frequent in patients on dialysis. Previous reports have indicated that onset and progression of AS were related to aging, hypertension, diabetes, or lipid disorders [6–8]. Some epidemiological studies in the general population have shown that the morbidity rate of AS in those over 75 years old is 2–4% [9]. Another general population study involving over 1.2 million individuals in Canada revealed that there were 20,995 patients who needed admission to hospitals or interventions for AS during 13 years of median follow-up [10]. On the other hand, patients on dialysis are more likely to develop AS because of hyperphosphatemia, anemia, and other factors. However, accurate morbidity rates and risk factors of AS in patients on dialysis remain unknown. Moreover, there are no large-scale observational studies of the association between AS in patients on dialysis and mortality or onset of cardiovascular (CV) events. Hence, we will examine whether morbidity of AS in patients on dialysis is associated with mortality, using the database of the Tokai Aortic Stenosis Cohort in Patients on Dialysis. We believe this is the first study to evaluate this association. We will consider the following hypotheses in this study: 1) The prevalence of AS is higher in dialysis patients than in the general population. 2) New onset and development of AS are associated with traditional risk factors including aging and comorbidity of diabetes. 3) New onset and development of AS are associated with factors that are specific for dialysis such as hyperphosphatemia, hypercalcemia, and hyperparathyroidism. 4) Outcomes in AS patients are poorer than in patients without AS at baseline. 5) Outcomes are poorer according to AS stages.

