### Patient characteristics and data at the time of enrollment (baseline)

Baseline is defined as the time at which echocardiography is performed for the first time from July 2017 to June 2018. We will review the following: 1) age, sex, dialysis vintage, and original kidney disease, blood pressure, and resting heart rate; 2) comorbidities including diabetes mellitus and malignancy; 3) medical history including hospitalization because of heart failure within one year, coronary heart disease, aortic disease, stroke, peripheral artery disease, malignancy, and history of parathyroidectomy; 4) medication including renin-angiotensin blockers, calcium channel blockers, β blockers, vitamin D receptor activators, calcimimetics, phosphate binders, and warfarin; 5) laboratory data including hemoglobin, platelet count, and serum albumin, alkaline phosphatase, uric acid, urea nitrogen, creatinine, adjusted calcium, phosphorus, magnesium, intact parathyroid hormone (PTH), ferritin, and C-reactive protein levels.

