### Echocardiography measurements

Transthoracic echocardiography will be performed by using commercially available ultrasound systems owned by each facility during enrollment and the follow-up period every year by an experienced technician. All parameters will be assessed with B mode or tissue Doppler imaging. The investigator will be blinded to clinical data. Findings will be confirmed by a cardiologist. The parameters used for evaluation of aortic valve are mean pressure gradient (mPG) between left ventricle and ascending aorta, aortic valve area (AVA), and maximum aortic jet velocity (aortic Vmax). Doppler echocardiographic measurements will include the peak and transaortic mPG using the simplified Bernoulli equation, and the AVA using the standard continuity equation or planimetry method in most participating facilities. Continuous wave Doppler will be used at multiple windows to obtain the maximal jet velocity over the aortic valve as well. In addition to the AS parameters, we will measure various parameters including left ventricular ejection fraction, left ventricular mass index, left atrial diameter, and E/E’. We will also examine aortic valve calcification.

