### Definition and classification of AS

We will diagnose AS using the following criteria based on the 2014 American Heart Association/ American College of Cardiology (AHA/ACC) Guideline for the Management of Patients with Valvular Heart Disease: 1) mPG > 20 mmHg, or 2) AVA < 1.0 cm2, or 3) aortic Vmax > 2.0 m/s [11]. We will evaluate stages A to D of AS according to the AHA/ACC Guideline. We will compare patient profiles, laboratory data at baseline, and outcomes including all-cause mortality and CV events among patients 1) with or without AS, and 2) 4 groups by stages.

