### Statistical processing

We will use SPSS statistics version 24 and the Easy R program [12] for statistical processing. Patient characteristics and baseline data will be compared between those with or without AS and those classified by AS stages using an unpaired t-test, analysis of variance for continuous variables, and Fisher’s exact test for nominal variables. We will compare incidence of all-cause mortality, CV events, CV-related mortality, infection-related mortality, and new onset of AS by using the log-rank test for Kaplan-Meier curves. The factors that contribute to all-cause mortality, CV events, CV-related mortality, infection-related mortality, and new onset of AS will be examined using univariate regression analysis. We will conduct multivariate Cox proportional hazards analysis using models with adjustment for some variables including age, gender, and factors that will be extracted as significant variables by univariate analysis. We will also examine factors contributing to annual change rates of mPG, AVA, and aortic Vmax with multiple regression analysis by using models. Continuous variables will be expressed as the mean and standard deviation, or the median and interquartile range, and categorical variables will be presented as a percentage. *P*-values less than 5% will be considered statistically significant.

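### The Cox model for new onset of AS fixes only age and gender; baseline aortic Vmax, mPG and AVA, whose cut-offs define onset, are neither named covariates nor named screening candidates

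*Protocol article*

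**What the plan says.** All references are to the protocol article.

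- **Outcome.** The Definition and classification of AS section diagnoses AS when any one of three limits is crossed: one on mPG, one on AVA, and "3) aortic Vmax > 2.0 m/s". The Outcomes section lists new onset of AS among the study outcomes.
- **Measurement.** Under Echocardiography measurements, all three quantities are taken "during enrollment and the follow-up period every year by an experienced technician". The baseline section ties baseline to the same examination: "Baseline is defined as the time at which echocardiography is performed for the first time from July 2017 to June 2018". The items it then lists for review contain no echocardiographic value.
- **Analysis.** Statistical processing first screens factors one at a time for each event outcome: "infection-related mortality, and new onset of AS will be examined using univariate regression analysis". It then plans multivariable Cox regression using "models with adjustment for some variables including age, gender, and factors that will be extracted as significant variables by univariate analysis". No outcome is exempted, so death and new onset of AS share one covariate rule. The threshold is 5% ("values less than 5% will be considered statistically significant").
- **Purpose.** Hypothesis 3 in Backgrounds reads: "New onset and development of AS are associated with factors that are specific for dialysis such as hyperphosphatemia, hypercalcemia, and hyperparathyroidism". Hypothesis 2 makes the corresponding statement for traditional risk factors.

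No section names baseline Vmax, mPG or AVA as a covariate, or says which variables are screened.

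**The concern.** New onset of AS differs from the other event outcomes. It is the first time a continuous quantity, already known at entry, is found beyond a fixed limit. How far a patient starts from that limit largely decides whether and when it is crossed. A rule that suits death does not automatically suit this outcome.

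The article itself gives reason to expect candidate factors to be linked to the starting value. Its section on risk for onset and development of AS says that fluid overload, anemia and access-related cardiac output raise the speed of flow through the valve. The Subjects section requires at least 12 months on dialysis, so such exposures act before baseline. A factor can therefore go with a high starting Vmax and appear to contribute to onset without affecting change after baseline.

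The stakes are the answers to hypotheses 2 and 3. The article also expects its results to lead to a treatment strategy. The Limitations section mentions baseline differences between groups and differing echo devices, but not this issue.

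**Working it through.** **No figure to reproduce.** The 2400 is an expected count of consecutive cases. The article gives no event rate, effect size or Vmax distribution, so the size of the effect has to be explored under assumptions.

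**Distance to the cut-off.** From the article: limit 2.0 m/s, echocardiography at 12, 24, 36, 48 and 60 months. Assumed mean rise: 0.05 m/s per year.
- Start 1.95 m/s: 2.0 − 1.95 = 0.05 m/s to go; 0.05 / 0.05 = 1 year.
- Start 1.2 m/s: 2.0 − 1.2 = 0.8 m/s to go; 0.8 / 0.05 = 16 years, against 5 years of follow-up.

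**Simulation model.** True Vmax of patient i at year k is v_i(k) = v_i(0) + s_i·k, and each echo adds random error. Onset is the first yearly echo above 2.0 m/s; death censors. The factor is x = ρz + √(1 − ρ²)·e, where z is standardized baseline Vmax and e is noise. It does not enter the slope s_i, so its true effect on progression is zero. Each setting has 150 cohorts, analyzed by Cox regression at two-sided 5% (two-sided is assumed; the article does not say).

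| Assumed input | Set A | Set B |
|---|---|---|
| Patients | 2000 free of AS | 2400 enrolled, about 2196 at or below 2.0 m/s |
| Baseline Vmax, mean (SD), m/s | 1.45 (0.25) | 1.5 (0.35) |
| Yearly rise, mean (SD), m/s | 0.05 (0.05) | 0.05 (0.06) |
| Echo error SD, m/s | 0.05–0.10 | 0.10 |
| Yearly mortality | 10% | 8% |
| Onsets | about 270–310 | about 482 |
| Model without Vmax | factor alone | factor, age, gender (age correlated 0.3 with baseline Vmax) |

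The comparison model adds measured baseline Vmax in each set.

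**Share of cohorts in which the factor is significant (mean hazard ratio per SD in brackets)**

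| ρ | A, without Vmax | A, with | B, without Vmax | B, with |
|---|---|---|---|---|
| 0 | – | – | 1% (1.003) | 3% (1.000) |
| 0.1 | 43–45% | 7–9% | 52% (1.094) | 4% (1.015) |
| 0.2 | 95–97% (about 1.25) | 7–15% (1.02–1.06) | 92% (1.193) | 8% (1.030) |
| 0.3 | 100% | 12–30% | 100% (1.313) | 17% (1.052) |

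A further variant with age in the model gave, at ρ = 0.2, 95–100% without baseline Vmax and 6–8% with it.

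**Precision.** The simulation standard error of a rate p is √(p(1 − p)/150). At p = 0.92 or 0.08 it is √(0.0736/150) = 0.022, so 8% is not distinguishable from the nominal 5%.

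**Sensitivity in set B at ρ = 0.2 (without against with baseline Vmax)**
- 600 enrolled: 41% against 5%. 1200 enrolled: 76% against 7%.
- Echo error SD 0: 94% against 3%. Echo error SD 0.20 m/s: 99% against 45%.

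**What the stated screen would do.** In set B, baseline Vmax was univariately significant in 100% of cohorts in every setting. At ρ = 0.2 the factor with no effect on progression passed the same screen in 96%. If both are screened, both normally enter and the columns with Vmax apply. If Vmax is not screened, the factor enters and the columns without it apply. The article does not settle which.

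**The case against.** A reader might infer that the plan leaves baseline Vmax out and will therefore report false contributors. The text does not support that. Its covariate list is open-ended, Vmax is measured at enrollment, and the univariate rule would almost certainly pick it up once it is a candidate. The absence of echo values from the baseline list proves little, because the next section lists them as measured at enrollment. A full candidate list may also sit in a document not shown. All of this stands, and it limits the point to what could happen.

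Set A's 95–97% comes from a model with the factor alone, which is not the planned final model. This also stands. Set B, with age and gender included, still gives 92%, so the two guaranteed covariates do not remove the effect.

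Progression has its own analysis: Statistical processing plans multiple regression on the yearly change in mPG, AVA and Vmax. This is true and softens the harm, but new onset remains a separate outcome with its own regression.

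The unadjusted association need not be wrong. The hypotheses speak of association, and a factor such as long dialysis vintage may truly have raised Vmax before baseline. Baseline Vmax would then lie partly on the causal path, and adjusting for it would remove part of a real effect. This stands, and it is why both estimates should be shown. For the same reason, forcing Vmax into every one-factor screening model would be preference and is not required.

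The simulations use only the Vmax criterion, although mPG or AVA can also define AS. Their rates are illustrative.

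**Conclusion.** The point holds as an inexpensive improvement. One covariate rule serves every event outcome, although onset of AS alone is defined by limits on quantities known at entry. The article neither fixes those baseline quantities in the model nor makes them candidates.

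If they are left out, factors that go with a starting value near the cut-off could be reported as contributing to onset. At an assumed correlation of 0.2 with baseline Vmax, a factor with no effect on progression is significant in about 92–100% of simulated cohorts without baseline Vmax and about 6–15% with it, at echo error SD 0.05–0.10 m/s. At SD 0.20 m/s the adjusted rate is still 45%. The correlation, Vmax distribution, progression, echo error and mortality are all assumptions; the rates depend on them, the direction does not.

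The documents do not show that Vmax will be omitted, nor that an estimate without it is invalid. What is missing is a commitment to which question the onset model answers.

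**What to change.** In Statistical processing, state that the multivariable Cox model for new onset of AS is fitted in patients free of AS at baseline and includes baseline aortic Vmax as a continuous covariate whatever its univariate p-value, with baseline mPG and AVA where measured. Report the factor estimates with and without baseline Vmax, and say how each is read:
- with it, progression to AS from a given starting value;
- without it, the overall association, including effects that acted before baseline.

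The one-factor screening models can stay as planned.

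Cost: one sentence and a covariate already collected. The adjusted hazard ratio answers a narrower question, and echo measurement error leaves some residual confounding, which the report should acknowledge.

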## Abstract

**Background:**

Aortic stenosis (AS) is common in patients on dialysis as well as in the general population. AS leads to difficulty with dialysis therapy because of unstable conditions such as intradialytic hypotension due to low cardiac output. However, the precise morbidity rates and risk factors of AS in patients on dialysis are unknown. Moreover, there are no large-scale observational studies regarding the association between AS in patients on dialysis and mortality. Therefore, we will investigate whether morbidity of AS in patients on dialysis is associated with mortality.

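### Choosing Cox covariates by univariate significance leaves the adjusted AS hazard ratio without a defined meaning, and it may be attenuated if cardiac mediators enter

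*Protocol article*

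**What the plan says.** The question is whether AS matters for prognosis. The abstract of the protocol article says "we will investigate whether morbidity of AS in patients on dialysis is associated with mortality", and hypothesis 4 in Backgrounds reads "Outcomes in AS patients are poorer than in patients without AS at baseline". Hypothesis 5 extends this to AS stages.

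Under Statistical processing, contributing factors for all-cause mortality, CV events, CV death, infection death and new-onset AS "will be examined using univariate regression analysis". The multivariable Cox models then use "adjustment for some variables including age, gender, and factors that will be extracted as significant variables by univariate analysis". The only threshold given is that P-"values less than 5% will be considered statistically significant". No separate adjustment rule is given for the AS comparison.

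The baseline section lists "medical history including hospitalization because of heart failure within one year" among the items collected. Echocardiography measurements adds "left ventricular ejection fraction, left ventricular mass index, left atrial diameter" and E/E', and then "We will also examine aortic valve calcification". The article does not say which of these are candidates for the screen, and it excludes none.

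**The concern.** One rule is used for two jobs. Screening by P-value is a common, if crude, way to look for prognostic factors. Estimating what AS does to survival in an observational cohort is a different task: it needs the variables that influence both AS and outcome, and it needs a decision about variables that AS may itself change.

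Two things can go wrong.

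- **Mediators can enter.** The abstract attributes intradialytic hypotension in AS to low cardiac output, so the authors recognise a route from AS through cardiac function. Markers on that route predict death strongly and would pass a univariate screen. Adjusting for them removes part of the effect that hypotheses 4 and 5 are about.
- **Confounders can be left out.** Apart from age and gender, a variable stays only if it is significant alone for that outcome. A real confounder can fail this test when its unadjusted association is weak or is masked by another variable.

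The Limitations section concedes baseline differences between groups, and the Cox model is the adjustment described for them. If its covariate set has no stated causal logic, a reader cannot say what the adjusted AS hazard ratio estimates.

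**Working it through.** **Is there a figure to reproduce?** No. The article gives no hazard ratio, event count or power. The sample size of over 2400 is the number of consecutive cases expected in a year. The effect of the rule was therefore examined by simulation.

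**Inputs from the protocol article:** 2400 patients, about 5 to 6 years of follow-up, age and sex always in the model, screen at P < 0.05.

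**Assumed inputs:** AS prevalence 10% and 30%, and a death rate that gave about 840 to 910 deaths (840/2400 = 35%; 910/2400 = 38%). One cardiac marker has effect *a* of AS on the marker and effect *b* of the marker on the log hazard. There were 100 replicates per setting. The SD of the log hazard ratio across replicates was 0.06 to 0.10, so the mean carries a Monte Carlo error of at most about 0.10/√100 = 0.01 on the log scale.

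**Does such a marker pass the screen?** Yes, in 100% of replicates in every setting.

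**What happens to the AS hazard ratio (HR)?** Where the marker is a mediator, the total effect built into the model is the direct HR × exp(*a* × *b*). Ranges cover the two prevalences.

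| Role of the marker | HR built in | Age and sex only | Marker added by the screen |
|---|---|---|---|
| Mediator, weak (*a* 0.3, *b* 0.3) | direct 1.30; total 1.30 × e^0.09 = 1.42 | 1.40–1.41 | 1.30–1.31 |
| Mediator, strong (*a* 0.8, *b* 0.5) | direct 1.30; total 1.30 × e^0.40 = 1.94 | 1.83–1.84 | 1.30 |
| Mediator (*a* 0.5, *b* 0.3) sharing an unmeasured cause with death | direct 1.30; total 1.30 × e^0.15 = 1.51 | 1.41–1.43 | 1.16 |
| Not a consequence of AS; its cause also raises AS | 1.50 | 1.60–1.61 | 1.49 |
| Not a consequence of AS; its cause lowers detection of AS | 1.50 | 1.30–1.31 | 1.50–1.51 |
| Prognostic, unrelated to AS | 1.50 | 1.41–1.45 | 1.50–1.53 |

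The age-and-sex column falls below the built-in total, and the last row rises on adjustment, partly because leaving out a strong prognostic variable pulls a Cox hazard ratio toward 1 even without confounding.

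- **Mediator rows.** The share of the log hazard ratio lost is 1 − ln 1.30/ln 1.40 = 22% (weak) and 1 − ln 1.30/ln 1.84 = 57% (strong). In the third row the result, 1.16, is below even the direct effect of 1.30, so it is neither a total nor a direct effect.
- **Confounder rows.** The marker-adjusted estimate is the right one, and leaving the marker out is the error.
- **What the rule sees.** The marker passed the screen every time in all six rows, so the screen gives no information about which row applies.

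**Valve calcification.** Modelled as an upstream cause of AS with no separate effect on death, it left the HR at 1.50–1.51. It only widened the spread of the log estimate: from 0.098 to 0.103 at 10% prevalence, and from 0.070 to 0.077 at 30%.

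**Dropping confounders.** This was not simulated. As a guide, with *D* deaths a factor reaches two-sided P < 0.05 about half the time when its log HR per SD is 1.96/√*D*. With 840 deaths this is 1.96/28.98 = 0.068, an HR of 1.07 per SD. Below that, a confounder of all-cause death is more likely dropped than kept. The bar is higher for outcomes with fewer events, such as infection death.

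**The case against.** The strongest reply is that the article lists what is collected, not what is screened. It names no echocardiographic variable as a Cox covariate and leaves the final set open. That stands: the rule permits these markers but does not say they enter.

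The causal order is also unsettled. The markers are measured with, or relate to a time before, the echocardiogram that classifies AS. In dialysis patients, fluid load, anemia and access flow, which the Discussion names as drivers of the valve lesion, could plausibly affect the heart as well. If so, adjustment removes bias. That also stands, and it rules out a fix that simply bans cardiac measures.

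A reader might infer more than the documents support:

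- **That the hazard ratio is biased toward 1.** This holds only if the markers are mediators and the total effect is wanted.
- **That valve calcification is a consequence of AS.** The Discussion places it among the processes behind onset and development of AS.
- **That AS itself is dropped when not significant.** The text does not say AS is forced in, but a model described as adjusted for covariates can equally be read as keeping its exposure.
- **That chance covariates are a known problem.** The article lists 34 baseline items and 5 further echocardiographic ones. If 30 were null and independent, 30 × 0.05 = 1.5 would enter by chance, but nothing supports 30, and no resulting harm to the AS estimate has been shown.
- **That confidence intervals are too narrow.** Selection can do this, but no calculation here shows it.

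Different covariates for different outcomes are not an error in themselves, since no comparison of hazard ratios across outcomes is planned.

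The objection does not rescue the rule. The sentence is a stated method, not a detail left to an analysis plan, and a later plan would have to contradict it to put it right.

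**Conclusion.** The concern holds in a limited form. For hypotheses 4 and 5, selection by univariate significance does not exclude variables that may lie between AS and death, and it can discard confounders. The adjusted AS hazard ratio therefore has no clear reading as a total or a direct effect.

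If the cardiac markers are mediators, the hazard ratio may be attenuated. In the assumed settings the loss ran from about a fifth to more than half of the log hazard ratio. If they are confounders, the screened model may be nearer the truth than one without them. The size and direction cannot be derived from the documents: they depend on the markers' causal role, and every path strength, prevalence and event count used here is an assumption. What does not depend on those assumptions is that a P-value against the outcome cannot tell these roles apart. The sentence should be changed, but it does not show that the study's answer will be wrong.

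**What to change.** Rewrite the adjustment sentence under Statistical processing so that it separates the two aims.

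1. **AS and outcome (hypotheses 4 and 5).** State that AS, or AS stage, is always in the model. Replace the screen with confounders pre-specified on subject grounds from the baseline list, for example: age, sex, dialysis vintage, primary kidney disease, diabetes, blood pressure, prior coronary disease, stroke or peripheral artery disease, malignancy, albumin, C-reactive protein, hemoglobin, phosphorus, calcium and PTH.
2. **Cardiac measures.** Add ejection fraction, left ventricular mass index, left atrial diameter, E/E' and recent heart-failure admission in a second, labelled model. The AS hazard ratio is then shown with and without them, and the reader can see how far it depends on their assumed role.
3. **Valve calcification.** Treat it as part of the AS disease process, not as a consequence of AS.
4. **Screening.** Limit univariate screening to risk-factor analyses labelled exploratory.

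The cost is a rewritten paragraph and one more reported model. The variables are already collected. The analysts give up data-driven choice of covariates for the AS estimate.
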